### Protocol Design for the Substudy

A total of 6 (27.3%) participants for the substudy were drawn from the participant pool (N=22) for the main study. The 6 participants visited the exercise physiology laboratory on a designated day. Upon their arrival, a research team member explained the process to them. The participants were then allocated to either the S-C group or the S-T group, after which they spent approximately 5 minutes familiarizing themselves with either the S-C or the S-T equipment. During the indirect calorimetry measurement, a mouthpiece connected to a metabolic cart (Parvo Medics True One 2400) was attached to the participant’s head. The participant breathed through the mouthpiece while remaining seated for 5 minutes. The metabolic cart collected breath-by-breath expired air and recorded the rate of oxygen consumption (VO_2_) and METs. After baseline measurements were recorded, the participants rested for about 5 minutes. Subsequently, they underwent an indirect calorimetry session while doing S-C or S-T at a self-selected pace with minimal or negligible applied resistance for 5 minutes each. The total duration of the session averaged approximately 40 minutes. Figure 2 shows a schematic illustration of the substudy.

**Figure 2 figure2:**
[figure not shown]
Schematic representation of the substudy. MET: metabolic equivalent; VO2: oxygen consumption.

### Protocol Design for the Main Study

Participants were allocated by the researcher to either the S-C or the S-T group in a 1:1 ratio using a coin toss for the first assignment (random start), followed by a prespecified alternating allocation sequence based on enrollment order. Within each assigned modality, outcomes were assessed repeatedly across prespecified time points (t_0_, t_1_, t_2_) and across two occasions (the experimental LIPA condition and the corresponding modality-matched passive control condition). As allocation concealment was not implemented and subsequent assignments were predictable, this approach is described as sequential (quasi-random) allocation rather than full randomization. Figure 3 shows the timeline of enrollment, intervention, and assessment phases of the main study.

**Figure 3 figure3:**
[figure not shown]
Schematic representation of the main study. BP: blood pressure; fNIRS: functional near-infrared spectroscopy; HR: heart rate.

### Intervention

#### S-C Experimental Condition

Participants assigned to the S-C intervention group cycled on the EZ Tone Chair at a self-selected cadence against a minimal applied resistance for 5 minutes. The chair measures 57 × 39 × 76 cm^3^ in dimension and is equipped with toe cap foot pedals. Previous research in the same institution used it as an exercise tool for reducing sedentary behavior in desk-bound participants [33]. In addition, participants were asked to rate their exertion levels on the 1-10 Borg RPE scale at every 1-minute interval.

#### S-T Experimental Condition

Participants assigned to the S-T intervention group stood on the AIBI Massage Body Twister and twisted their torso along the transverse plane in an alternating clockwise and counterclockwise direction with even arm swings for balance and at a comfortable cadence (about 2 seconds for a full left-right trunk twist) for 5 minutes. The twister is a compact piece of equipment with a diameter of 35 cm and is portable, making it convenient for use in any setting. It has been used as an intervention method for reducing sitting time and investigating the weight loss effects in participants with obesity [40]. In addition, participants were asked to rate their exertion levels on the 1-10 Borg RPE scale at every 1-minute interval.

### Intervention Delivery and Fidelity

Interventions were delivered under direct supervision of a trained research team member to ensure standardization and participant safety. Both S-C and S-T groups received the same brief standardized instructions regarding posture, cadence, and safety before they started the 5-minute bout. Perceived exertion was recorded at 1-minute intervals using the Borg RPE scale to monitor intensity and support fidelity to LIPA.

Participants in the control groups spent a modality-matched passive control period with no structured physical activity (passive sitting on a chair or standing still) for the same 5-minute duration. Outcome assessments were conducted at identical time points as in the interventions. The modality-matched passive control conditions were selected to match the session duration and posture as closely as possible; however, they were not designed as sham interventions and therefore may not have adequately controlled for posture-related arousal, expectancy effects, or other context-related cues (eg, awareness of movement and perceived exertion).

Any protocol deviations and adverse events were documented.

### Key Outcome Measures

#### Primary and Secondary Outcomes

The primary endpoint of the main trial is the within-person intervention-control difference in the change in O_2_Hb in the bilateral DLPFC during cognitive task performance from baseline (t_0_) to posttest 1 (t_1_). The DLPFC O_2_Hb metric is defined as the bilateral DLPFC region-of-interest average, calculated as the baseline-corrected mean O_2_Hb during cognitive task performance at each time point.

Key secondary outcomes include (1) persistence of the O_2_Hb response posttest 2 (t_2_), (2) cognitive performance on the n-back test and the SCWT (accuracy and response time, as applicable), (3) HHb in the same DLPFC region (supportive physiological indicator), (4) BP and HR, and (5) symptom-based outcomes (eg, subjective daytime sleepiness and back pain measures).

#### Functional Near-Infrared Spectroscopy

fNIRS is based on the principle that most biological tissues are transparent to near-infrared light (NIR), while O_2_Hb and HHb better absorb NIR light in the 700-900 nm spectrum. fNIRS uses the modified Beer-Lambert law to measure the absorption rate of these hemoglobin species at two different NIR wavelengths between transmitter and receiver pairs placed on the scalp. In this study, an eight-channel portable continuous-wave NIRS system (Octamon, Artinis Medical Systems) was used to measure fNIRS signals during the n-back test and the SCWT. Hemodynamic responses were recorded from the bilateral DLPFC using eight transmitters and two receivers (one receiver receiving from four transmitters on each hemisphere; see Figure 4) over the forehead region, with each receiver measuring time-multiplexed NIR light from four surrounding transmitters that were 3 cm apart, resulting in eight data channels. All signals were sampled at 10 Hz. A MATLAB-based toolbox was used to accurately estimate the spatial brain mapping of the electroencephalography (EEG) 10-20 system onto associated Brodmann areas, identifying the left and the right DLPFC as the regions of interest. Following data collection, the fNIRS data will be processed using the HOMER3 MATLAB toolbox with the following pipeline: (1) conversion to optical density changes, (2) removal of low signal-to-noise channels, (3) motion artifact detection and correction, (3) bandpass filtering, and (4) conversion to concentration changes using the modified Beer-Lambert law, with block averaging to obtain the average change across three trials for each cognitive task condition.

**Figure 4 figure4:**
[figure not shown]
Illustration of the optode montage used indicating brain measurements using fNIRS (blue color: transmitters; yellow color: receivers). fNIRS: functional near-infrared spectroscopy.

#### n-Back Test

The n-back test is a cognitive assessment tool used to evaluate working memory capacity and cognitive inhibition [41]. It has also been widely used as a training tool for enhancing working memory [42,43]. During the n-back test, participants were shown a sequence of visual stimuli in the form of digits from 0 to 9 and were asked to indicate whether the current stimulus shown matched the one presented n characters earlier by pressing the designated letters on the keyboard (eg, letter “F” to indicate a match and “J” to indicate a mismatch). For this study, the 1-back and 2-back tests were adopted. In the 1-back test, participants were required to recall and indicate whether the current digit shown matched the previous digit, whereas in the 2-back test, participants indicated whether the current digit shown matched the second-last digit presented earlier. The n-back test consists of three blocks of 1- and 2-back tasks. A practice block was added to the baseline pretest, where participants were given 20 stimuli (letters) to familiarize themselves with the process before moving on to the actual test. The actual test consisted of three blocks with 30 stimuli (letters). The test began with a centered fixation cross on-screen for 500 ms, followed by the stimulus in that location for 1000 ms, followed by a 500 ms interstimulus interval. The *accuracy* (number of correct recalls) and *response time* (speed of recall) were assessed at the end of each block. The study design entailed participants to undergo the n-back test thrice (baseline, posttest 1, and posttest 2) on two occasions (experimental condition and waitlist control condition). Changes in the n-back test score from baseline to posttests 1 and test 2 were measured.

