#### Study Hypotheses

We hypothesize that compared with the modality-matched passive control, the 5-minute LIPA intervention will produce a greater t_0_-to-t_1_ change in DLPFC O_2_Hb during cognitive task performance (primary endpoint). We further hypothesize that O_2_Hb changes may persist at t_2_ and that cognitive performance (n-back test and SCWT accuracy/response time) may improve following the intervention (key secondary outcomes).

The hypotheses are as follows:

Hypothesis (H)1 (hemodynamics): Compared with the modality-matched control (passive sitting), both S-C and S-T are associated with higher DLPFC O2 Hb (primary) and corresponding changes in HHb (supportive) during cognitive task performance at t1 and/or t2 relative to t0.H2 (cognition): Compared with the corresponding modality-matched control, both S-C and S-T will result in improved working memory and inhibitory control performance (eg, n-back test and SCWT outcomes) at t1 and/or t2 relative to t0.H3 (physiological and symptoms): Compared with the corresponding modality-matched control, both S-C and S-T will lead to favorable acute changes in BP/HR and reduced subjective daytime sleepiness and back pain at t2 relative to t0.

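### n-back accuracy is a count of correct match/mismatch key presses, so it reflects the tendency to answer 'match' as well as memory, yet H2 reads it as working memory

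*Protocol article*

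**What the plan says.** All references are to the protocol article; no separate analysis plan is at hand.

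- **Response format (n-Back Test).** Each stimulus is answered with one of two keys: "letter “F” to indicate a match and “J” to indicate a mismatch". Both 1-back and 2-back are used.
- **Length (n-Back Test).** "The actual test consisted of three blocks with 30 stimuli (letters"). The share of stimuli that are matches is not given.
- **Score (n-Back Test).** "The *accuracy* (number of correct recalls) and *response time* (speed of recall) were assessed at the end of each block". The quantity analysed is a change score: "Changes in the n-back test score from baseline to posttests 1 and test 2 were measured".
- **Status (Primary and Secondary Outcomes; Statistical Analysis).** The key secondary outcomes include "cognitive performance on the n-back test and the SCWT (accuracy and response time, as applicable"). The Statistical Analysis section puts these endpoints in the Holm-Bonferroni family.
- **Interpretation (Study Hypotheses, H2).** Both modalities are expected to give "improved working memory and inhibitory control performance (eg, n-back test and SCWT outcomes) at t1 and/or t2 relative to t0".

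The article does not separate hits from false alarms and names no sensitivity or bias index.

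**The concern.** In a yes/no recognition task two things determine how many answers are right: how well the participant tells matches from mismatches (sensitivity), and how much evidence the participant wants before pressing 'match' (criterion). The stated count combines them. If all items are counted and matches are the minority, a participant who becomes more reluctant to press 'match' usually gains. If only correctly detected matches are counted, which the word recalls would also allow, a participant who becomes more willing to press 'match' gains, and pressing that key throughout scores perfectly.

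At stake is the working-memory half of H2. A condition difference in the count could be reported, with family-wise error control, as better or worse working memory when only response style had moved. Multiplicity control does not help, because it limits chance findings and not a mislabelled construct.

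**Working it through.** The protocol gives no figure for n-back accuracy, so there is none to reproduce. The check asks how far the stated score moves when memory is held fixed.

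**Inputs from the protocol:** two-key response; 30 stimuli per block, three blocks; accuracy as a count correct.

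**Assumptions, not in the protocol:** equal-variance signal-detection model; d' = 1.5, 2 or 3; criterion c moved from 0 to 0.5 (towards 'mismatch'); match proportion p = 0.10 to 0.50.

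**Formulas**
- Hit rate H = Φ(d'/2 − c)
- Correct-rejection rate CR = Φ(d'/2 + c)
- All-item count per 30 = 30 × [p·H + (1 − p)·CR]

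**Step 1, rates at d' = 2**
- c = 0: H = Φ(1) = 0.841, CR = Φ(1) = 0.841
- c = 0.5: H = Φ(0.5) = 0.691, CR = Φ(1.5) = 0.933

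**Step 2, all-item count at d' = 2**

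| p | c = 0 | c = 0.5 | change |
|---|---|---|---|
| 0.10 | 25.24 | 27.27 | +2.03 |
| 0.20 | 25.24 | 26.55 | +1.31 |
| 0.33 | 25.24 | 25.60 | +0.36 |
| 0.50 | 25.24 | 24.37 | −0.87 |

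Worked row, p = 0.10: 30 × (0.1 × 0.691 + 0.9 × 0.933) = 30 × 0.909 = 27.27.

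The sign turns where the loss in hits equals the gain in correct rejections. H falls by 0.150 and CR rises by 0.092, so p = 0.092/(0.092 + 0.150) = 0.38.

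**Step 3, other sensitivities, same shift**
- d' = 1.5: 23.20 to 25.06 at p = 0.20; 23.20 to 23.90 at p = 0.33
- d' = 3: 28.00 to 28.50 at p = 0.20; 28.00 to 27.97 at p = 0.33

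**Step 4, hits-only reading at d' = 2.** The score falls from 84.1% to 69.1% of matches, whatever p is. A shift the other way, c from 0 to −0.5, raises it from 84.1% to 93.3%.

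**Step 5, what d' does under the same shift.** True d' is unchanged by construction. Estimated from 90 items with the log-linear correction (0.5 added to each count of hits and false alarms, 1 to each denominator), simulated mean d' goes from 1.95 to 1.98 at p = 0.10 and from 1.98 to 1.99 at p = 0.20.

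**Step 6, does the shift reach the treatment contrast?** The analysis compares change from t0 between a participant's two visits. A criterion that is the same at every assessment adds no false difference. Nor does one that drifts equally at both visits when sensitivity is the same at both. Only a drift that differs between the intervention and control visits creates a false difference. The protocol gives grounds to think this possible. H3 predicts less sleepiness after the bout. Intervention Delivery and Fidelity concedes that the control may not have handled posture-related arousal and expectancy. Strengths and Limitations accepts that lack of blinding may alter engagement and effort.

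**The case against.** The case on the other side is substantial, and much of it stands.

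- **Size and direction are assumed.** Neither d' = 2 nor the 0.5 shift has a source in the protocol, and at 33% matches with d' = 3 the effect is essentially nil. This stands: it limits what can be said about magnitude. That the score mixes two things does not depend on it.
- **The within-person design removes stable bias.** This stands. The protocol shows no evidence of a differential criterion shift, and its remark about engagement and effort is not a statement about match/mismatch bias. The error need not cancel; it cannot be said that it does not.
- **A count correct is an ordinary n-back score, and d' can be less sensitive.** This stands as an argument against replacing the count. Simulating a true gain from d' = 2.0 to 2.5 with 90 items, 10% matches and c = 0 gives a standardised effect of about 1.5 for the count and 0.96 for d'; at c = 0.5 it is about 1.2 and 0.97.
- **Late substitution looks like outcome switching.** This stands. Trial Status says data collection ended in December 2024 and preliminary analyses are under way.

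A reader might also infer three stronger points that the document does not support. First, that random digits from 0 to 9 imply 10% matches, so that 27 of 30 is a floor: random drawing is not stated, and 27 would be the score from pressing 'mismatch' throughout, whereas random pressing scores 15. Second, that response time includes incorrect answers: the article does not say which trials enter, and an article may leave that to the full plan. Third, that the condition is known to shift the criterion.

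**Conclusion.** The concern holds as a matter of construct validity for one key secondary endpoint. The scoring rule is stated, not left open, and under either reading of it (all correct answers, or correctly detected matches) the count can move with memory unchanged. For a criterion shift from 0 to 0.5 at d' = 2, the all-item count moves by between −0.9 and +2.0 of 30 for match rates from 50% down to 10%, and the hits-only score by −15 percentage points. These figures are conditional on the signal-detection model, the chosen shift and an undisclosed match rate. Bias in the treatment contrast further requires that the shift differ between visits, which is plausible here but not shown. The conclusion is therefore that the count alone cannot carry the working-memory claim, not that the n-back result will be wrong. The primary endpoint is not touched.

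**What to change.** Keep the count of correct answers as the declared n-back accuracy endpoint, and say whether it covers all items or matches only. Then add, from the existing key-press logs:

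1. The match rate for 1-back and for 2-back.
2. Hit rate, false-alarm rate and d' at each time point and visit, separately for 1-back and 2-back, pooled over the blocks of each load, with the log-linear correction.
3. A reading rule for H2: improved working memory is claimed only if d' moves in the same direction as the count, and faster responses are not read as improvement when d' falls.

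Date the addition, label it as made after data collection, fix it before n-back results by condition are examined, and state whether anyone had already seen them.

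**Cost.** Rescoring and a short text change, with no new data, provided that item-level key presses were stored (likely for a computerised task, but not stated). The main drawback is that d' is noisier when matches are few, so the added condition makes a working-memory claim somewhat harder to support. If item-level data were not kept, the count should be reported as task performance, without the working-memory reading.

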#### Stroop Color and Word Test

The SCWT is a cognitive test widely used to assess the ability of an individual to inhibit cognitive interference that occurs when the processing of a specific stimulus feature is impeded by the simultaneous processing of another attribute of the same stimulus [44]. In this study, the test consisted of a series of color words (eg, “red,” “blue,” “green,” and “yellow”) printed in colored ink, with the font color sometimes matching the word and sometimes not. We adopted the incongruent condition, where participants were shown a sequence of stimuli in which the word text matched or did not match the color of the ink (eg, the word “red” could be printed in blue ink). Participants were required to indicate whether the word text matched the color of the ink by pressing the designated letter on the keyboard (eg, letter “F” to indicate a match and “J” to indicated a mismatch). The color of the words was displayed on the screen one at a time for 2000 ms. Participants were presented with six blocks of words, alternating between congruent and incongruent words. The test typically consists of multiple blocks (three or four) and records the *accuracy* of each response (number of correct texts and colors) and the *reaction time* (time taken to input a response). A practice block was added to the baseline pretest for familiarization like in the n-back task. Participants underwent the test thrice at different time points (ie, baseline, posttest 1, and posttest 2) on two occasions (experimental condition and waitlist control condition), and changes in the SCWT scores from baseline to posttests 1 and test 2 were determined.

#### BP and HR Measurement

Participants’ BP and HR were measured using the Vivo Watch BP HC-A04 (ASUSTek Computer Inc) worn on the wrist. With a pair of electrocardiography (ECG) and photoplethysmography sensors embedded in the watch, the Vivo Watch BP HC-A04 provides systolic and diastolic BP and HR readings. Previous studies have evaluated the validity of smartwatch-based BP-monitoring features, and validation evidence has also been reported for an ASUS VivoWatch series device against reference sphygmomanometer measurements [45]. Accordingly, BP readings in this study will be interpreted primarily for research monitoring (ie, within-participant comparisons across time points) rather than for clinical diagnosis. Measurements of BP and HR were taken at baseline, posttest 1, and posttest 2, and changes in the BP and HR readings from baseline to posttests 1 and 2 were determined.

#### Stanford Sleepiness Scale

The Stanford Sleepiness Scale (SSS) is a self-rating tool designed to evaluate changes in sleepiness on a 7-point scale, applicable at any time of day [44,46]. In this study, participants were asked to rate their level of sleepiness upon visiting the test site at baseline and posttest 2 by choosing a number and description that best described their state. The scale ranges from “feeling active, vital, alert, or wide awake” to “no longer fighting sleep, sleep onset soon, or having dream-like thoughts.” The SSS correlates well with task performance related to alertness [47], and it has been previously used to gather subjective sleepiness data among workers [48].

#### Oswestry Low Back Disability Questionnaire

The Oswestry Low Back Disability Questionnaire (OLBDQ) is a widely used tool for assessing functional abilities relating to low back pain. The self-reported questionnaire has been validated and its reliability tested, and it is used in different populations [49]. In this study, participants completing the OLBDQ were asked about how low back pain affects their ability to manage their everyday life. The different contexts in everyday life included in the questionnaire are (1) pain intensity, (2) personal care (washing, dressing), (3) lifting objects, (4) walking, (5) sitting, (6) standing, (7) sleeping, (8) social life, and (9) traveling. For example, regarding pain intensity, participants were asked to select the statement that best described their problem: “I have no pain at the moment,” “The pain is very mild at the moment,” “The pain is moderate at the moment,” The pain is fairly severe at the moment,” “The pain is very severe at the moment,” or “The pain is the worst imaginable at the moment.” For each section, the total possible score is 5, and each statement is marked with a score; for example, the first statement is marked with a section score of 0, the second statement is marked with a section score of 1, and so on until the sixth statement is marked with a section score of 5. There are nine application sections, yielding a total possible score of 45. A higher score is interpreted as more severe low back functional disability. In this study, the OLBDQ was administered at t_0_ and t_2_ during each visit to capture baseline and delayed responses; it was not administered at t_1_.

